#### 2.8.1 Primary clinical outcome

The *Revised Fibromyalgia Impact Questionnaire* (FIQR; Luciano et al., 2013) is a 21-item questionnaire (0–10 scale) which assesses the dimensions of physical dysfunction, overall impact of FM and severity of the symptoms (i.e., pain, energy, stiffness, sleep quality, depression, memory issues, anxiety, pain to the touch, balance problems, and increased sensitivity to noises, lights, smells, or temperatures), and is used to measure the impact of FM over the past week. This questionnaire is currently considered the “gold standard” for assessing functional impairment in patients with FM. A total score for FIQR ranging from 0–100 can be obtained by adding the 3 subscales, with higher scores indicating greater FM severity. The Spanish version of the FIQR has an excellent internal consistency (α = 0.91–0.95) (Luciano et al., 2013).

#### 2.8.2 Secondary clinical measures

- *Visual-analogue scale of perceived pain* (VAS-Pain; Serrano-Atero et al., 2002) in which patients indicate their pain during the last week on a 10 cm line (0 = No pain, 10 = Unbearable pain).

- *Visual-analogue scale of perceived energy/fatigue* (VAS-Fatigue; Serrano-Atero et al., 2002) in which patients indicate their fatigue during the last week on a 10 cm line (0 = Lots of energy, 10 = No energy).

- *Hospital Anxiety and Depression Scale* (HADS; Luciano et al., 2014a). HADS is used to quantify the severity of anxiety and depression symptoms. It consists of two dimensions (anxiety and depression) of 7 items each responding on a Likert scale of 4 points. Total scores of each scale (HADS-A and HADS-D) range from 0 to 21, where higher scores indicate greater symptom severity. The Spanish version of the HADS has demonstrated satisfactory internal consistency for anxiety (α = 0.83) and depression (α = 0.87) subscales inpatients with FM (Luciano et al., 2014b).

- The *Perceived Stress Scale*, short form (PSS; Herrero and Meneses, 2006) is a 4-item scale used to evaluate the degree to which respondents appraise situations as stressful in the last month with responses scored on a Likert scale between 0 = “never” and 4 = “very often,” and with total scores ranging from 0 to 16 for the short 4-item version of the scale. Higher scores indicate greater perceived stress. The Spanish version of the 4-item version of the PSS shows acceptable internal consistency (Cronbach’s α = 0.77).

- The *physical function subscale of the Short Form-36 Health Survey* (PF-SF-36; Alonso et al., 1995) is used to measure physical function. This dimension comprises a total of 10 items, which are answered on a Likert scale of 3 points. Total scores on each scale are transformed and can range from 0 to 100, with higher scores indicating better physical function. The Spanish version of the PF-SF-36 shows adequate internal consistency (α = 0.94).

- *Brief version of the Pittsburgh Sleep Quality Index* (B-PSQI; Sancho-Domingo et al., 2021). The PSQI is the most widely used questionnaire in research and clinical practice to assess sleep quality. The B-PSQI is a brief version of this measure including six questions about sleep quality. The Spanish version of the B-PSQI shows adequate internal consistency (α = 0.79).

- The *Multidimensional Inventory of Subjective Cognitive Impairment* (MISCI; Feliu-Soler et al., 2018) is a 10-item scale with a 5-point Likert scale (from 1 “Not at all/Never” to 5 “Very much/Always”) for assessing perceived cognitive dysfunction in FM during last week. It includes the cognitive domains: mental clarity, memory, attention/concentration, executive functioning, and language. The MISCI was developed through classical test theory and item response theory from cognitive functioning item banks that were developed as part of the Patient Reported Outcomes Measurement Information System (PROMIS). The Spanish version of the MISCI shows excellent internal reliability (α = 0.91).

- The *Central Sensitization Inventory, short form* (CSI; Nishigami et al., 2018) is the brief form of the CSI (Cuesta-Vargas et al., 2016), and consists of two parts: part A includes nine items scored from 0 to 4, with higher total scores reflecting increased central sensitization symptoms; part B (which is not scored) determines whether one or more specific disorders of central sensitization related to pathophysiology (i.e., restless legs syndrome, chronic fatigue syndrome, FM, temporomandibular joint disorder, migraine or tension headaches, irritable bowel syndrome, multiple chemical sensitivities, neck injury, anxiety or panic attacks, and depression) have been diagnosed before. Adequate internal consistency for the CSI-9 has been also reported (Cronbach’s alpha = 0.80).

#### 2.8.3 Cost-utility measures

- *Client Service Receipt Inventory* (CSRI; Vázquez-Barquero et al., 1997). The CSRI is a questionnaire for economic evaluation. The version used in this study is designed to retrospectively collect data on the use of health and social services during the previous 6 months.

- EuroQoL-5D-5L (EQ-5D-5L; Badia et al., 1999). The EQ-5D-5L is an instrument for assessing health-related quality of life. It consists of two parts: the first part assesses the individual’s difficulties in relation to mobility, self-care, pain/discomfort and anxiety/depression; and the second part assesses the patient’s current perceived health status on an analogue-visual scale from 0 (“the worst health you can imagine”) to 100 (“the best health you can imagine”).

#### 2.8.4. Process measures

- *Pain Catastrophizing Scale* (PCS; García-Campayo et al., 2008). The PCS is used to evaluate catastrophic thoughts associated with pain. It consists of three dimensions (e.g., rumination, magnification, and helplessness) with 13 items in total, which are answered on a Likert scale of 5 points. Total scores on each scale range from 0 to 52, with higher scores indicating more catastrophic thoughts. The Spanish version of the PCS shows adequate internal consistency (α = 0.79).

- *Psychological Inflexibility in Pain Scale* (PIPS; Wicksell et al., 2008). The PIPS is a 12-item scale that assesses psychological inflexibility in pain patients, and includes two factors: avoidance and cognitive fusion with pain. The items consist of different statements that are considered to be related to chronic pain, psychological inflexibility, suffering and disability (coherent with the ACT theory). All the items are rated on a 7-point Likert scale that ranges from “1 = never true” to “7 = always true”, with higher scores indicating more psychological inflexibility. The Spanish version of the PIPS (Rodero et al., 2013) shows adequate internal consistency (α = 0.90).

- *Tampa Scale for Kinesiophobia* (TSK; Gómez-Pérez et al., 2011). The TSK is a measure aimed at assessing fear of movement and comprises 11 items in a 4-point Likert scale with a total score ranging from 11 to 44, with higher scores indicating greater pain and fear of movement. The Spanish version of the TSK has an adequate internal consistency (α = 0.79).

- The *Revised Neurophysiology of Pain Questionnaire* (R-NPQ; Torres-Lacomba et al., 2021). The R-NPQ consists of 13 statements (True/False/I do not know) about pain neurophysiology and has been extensively used to assess pain biology knowledge. The R-NPQ score ranges from 0 to 13 (sum of all correct items), and can be also expressed as a rate of correctly answered items. Excellent internal consistency for the R-NPQ has been reported in Spanish samples (α = 0.87–0.92).

### 2.9 Other self-reported measures

- The *Patient Global Impression of Change (PGIC)* and the *Pain Specific Impression of Change* (PSIC) (Scott and McCracken, 2015) are measures to assess, respectively, self-perceived meaningful clinical change (on a 7-point Likert scale, from 1 = “Much better” to 7 = “Much worse”) in general or in the following specific domains: physical and social functioning, work-related activities, mood, and pain.

- Adapted version of Credibility/Expectancy Questionnaire (CEQ; Devilly and Borkovec, 2000). It is a 6-item questionnaire widely used to assess treatment expectancy as well as the credibility of the FIBRO-On and FIBRO-Out interventions. The first part of the CEQ comprises three items focused on therapy credibility (i.e., the extent to which the treatment appears a)logical and b) useful, and c) the confidence with which the treatment’s patient would recommend this one to a friend with the same health condition); and three more items evaluating expectations (i.e., the extent to which the patient thinks an improvement will happen as a consequence of the treatment; the extent to which the patient really feels that the intervention will reduce him/her symptoms, and the extent to which the patient really feels a symptom improvement will occur). After finishing the treatment, the patient’s opinion regarding the treatment received will be also gathered by using the second part of the CEQ which includes the same questions as in the first part of the CEQ but in past tense. The CEQ showed overall adequate internal consistency (α = 0.84–0.85) in a previous study in a similar clinical sample (Pérez-Aranda et al., 2019).

- An *ad hoc* item (i.e., *Have you experienced, during the course of the treatment, any unwanted symptom that you think might be directly or indirectly associated with the intervention?*) to check for the presence of adverse effects (e.g., headaches, dizziness, sleep problems, *etc.*) associated with the evaluated interventions. This measure has been used in a previous study (Pérez-Aranda et al., 2019) and will be administered both at 6-week and post-intervention assessments.

- Patients’ adherence evaluation to the FIBRO-On and FIBRO-Out programs. An *ad hoc* instrument (i.e., personal practice log) for the weekly recording of home practice will be developed to determine level of adherence to psychotherapeutic and therapeutic exercise recommended homework.

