### 2.8 Study measures

Assessment of outcome and process measures will be carried out at baseline, 6 weeks after starting treatment, at post-intervention (12 weeks) and at 6-month follow-up after starting the trial (follow-up. Cost-utility assessment will be conducted at baseline and at the follow-up and biomarkers evaluation at baseline and post-intervention. The research assistants in charge of the evaluations will be extensively trained by researchers (MS, [name]), who have broad experience in applying the study measures.

The following domains will be assessed (see Table 3 for a summary of assessments):- Socio-demographic questionnaire: gender, date of birth, marital status, cohabitation, educational level and employment status.- Clinical data: date of FM diagnosis, years with a FM diagnosis, comorbidity with other diagnosed medical/psychiatric conditions, type and dosage of current medication, weight and height.

**TABLE 3 T3:** Summary of the assessments in the RCT.

	Baseline	6 weeks	Post-intervention (12 weeks)	Follow-up (6 months)
Sociodemographic and clinical characteristics of the sample				
Sociodemographic data	X			
Clinical data	**X**			
Primary outcome measure				
FIQR	**X**	**X**	**X**	**X**
Secondary outcome measures				
VAS Pain	**X**	**X**	**X**	**X**
VAS Fatigue	**X**	**X**	**X**	**X**
HADS	**X**	**X**	**X**	**X**
PSS	**X**	**X**	**X**	**X**
PF-SF-36	**X**	**X**	**X**	**X**
B-PSQI	**X**	**X**	**X**	**X**
MISCI	**X**	**X**	**X**	**X**
CSI	**X**	**X**	**X**	**X**
PGIC/PSIC			**X**	
Process measures				
PCS	**X**	**X**	**X**	**X**
TSK-11	**X**	**X**	**X**	**X**
PIPS	**X**	**X**	**X**	**X**
R–NPQ	**X**	**X**	**X**	**X**
Cost-utility measures				
CSRI	**X**			**X**
EQ-5D	**X**			**X**
Other self-reported measures				
CEQ	**X**		**X**	
Perceived adverse effects of the interventions		**X**	**X**	
Fidelity evaluation (adherence of the therapists to the FIBROWALK guidelines)			**X**	
physiological markers				
Immune-inflammatory markers	**X**		**X**	
BDNF	**X**		**X**	

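### The one dedicated harms item described asks for symptoms the patient attributes to the intervention, so it cannot give a like-for-like comparison with TAU

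*Protocol article*

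**What the plan says.** Section 2.9 of the protocol article describes a single ad hoc item. It opens "Have you experienced, during the course of the treatment" and asks about "any unwanted symptom that you think might be directly or indirectly associated with the intervention". Its purpose is "to check for the presence of adverse effects (e.g., headaches, dizziness, sleep problems" and similar), and the effects sought are those "associated with the evaluated interventions". The item "will be administered both at 6-week and post-intervention assessments".

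Table 3 in section 2.8 has one matching row, "Perceived adverse effects of the interventions", marked at 6 weeks and at 12 weeks and left blank at baseline and 6 months. The row is not split by arm, and the article does not say whether TAU participants answer the item.

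Three other statements bear on it. Section 2.13 says that participants and therapists cannot be blinded. Section 2.6.1 offers the programme to TAU participants only when the study is over. Section 2.8.1 lists among the symptoms scored by the FIQR "pain, energy, stiffness, sleep quality, depression, memory issues, anxiety, pain to the touch, balance problems".

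**The concern.** The item combines two questions: whether a symptom occurred, and whether the programme caused it. Only the first can be compared across randomised arms. A TAU participant has received no study programme, so either has nothing to report or answers about usual treatment, which section 2.6.1 describes as mainly pharmacological. Neither answer matches what an active-arm participant is asked.

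Within the active arms, the count passes through the judgement of an unblinded patient with a fluctuating condition. Background symptoms may be blamed on the programme, which overstates harm. A real effect may be put down to fibromyalgia, which understates it. The net direction cannot be predicted.

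Both programmes include graded exercise and walking homework. The Discussion says that a format shown to be effective and cost-effective should become part of standard care. The trial has a randomised TAU arm that could inform the harm side of that judgement, and this item does not use it.

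**Working it through.** **Figures in the article.** There are none for harms: no expected rate, margin or precision. The only relevant inputs are the arm sizes in section 2.3, namely 75 per arm and an expected dropout of 20% to 25%. Evaluable numbers are then 75 × 0.80 = 60 and 75 × 0.75 = 56.25, taken as 56.

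**What the item can estimate.** Let p1 be the proportion in an active arm with a new or worsened symptom, p0 the same proportion in TAU, and a the share of active-arm participants with a symptom who attribute it to the programme. The target is p1 − p0. The item observes a × p1 in the active arm. In TAU it observes nothing that corresponds to p0.

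Illustration, with all rates assumed: p1 = 0.40, p0 = 0.30, a between 0.25 and 0.75.
- Observed active-arm proportion: 0.40 × 0.25 = 0.10 up to 0.40 × 0.75 = 0.30.
- True excess: 0.40 − 0.30 = 0.10.

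The observed figure can range from 10% to 30% while the true excess stays at 10 points. A larger sample does not help, because neither a nor p0 is measured.

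**What a neutral item would give.** The 95% half-width for the difference is 1.96 × √[(p1(1 − p1) + p0(1 − p0))/n]. With the same rates the numerator is 0.24 + 0.21 = 0.45.

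| Evaluable per arm | Calculation | Half-width |
|---|---|---|
| 75 | 1.96 × √(0.45/75) | 0.152 |
| 60 | 1.96 × √(0.45/60) | 0.170 |
| 56 | 1.96 × √(0.45/56) | 0.176 |

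A 10-point excess would therefore not be distinguished from zero. For 80% power at two-sided 0.05, the excess needed depends on the assumed TAU rate:

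| Assumed TAU rate | Excess needed at 75 per arm | Excess needed at 56 to 60 per arm |
|---|---|---|
| 10% | about 18 points | about 20 to 21 points |
| 30% | about 22 points | about 25 to 26 points |
| 50% | about 22 points | about 25 points |

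**What other measures already cover.** Table 3 schedules the FIQR, VAS pain, VAS fatigue, HADS, PF-SF-36 and B-PSQI at all four assessments, with no arm excluded. Section 2.11.1 analyses the primary and secondary endpoints by group and time on an intention-to-treat basis. None of these measures asks for attribution to the programme. The CSRI records service use over the previous 6 months at baseline and at 6 months, and section 2.11.3 costs emergency consultations and hospital admissions. Average worsening and medical visits can therefore be compared with TAU. A fall, a strain or a new symptom in an individual would not be identified.

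**The case against.** The strongest case against has several parts.

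- **This is a condensed article.** The ethics committee approved a study protocol that is not shown, and adverse-event reporting may be set out there. This stands. A reader might infer that the trial has no other harms collection, but the article cannot support that. The point is limited to the dedicated measure it describes. Its wording and timing are stated, and no later analysis plan can recover answers that were never requested.
- **Overlapping symptoms are measured neutrally in every arm.** This stands in part. A reader might conclude that harm cannot be told from fibromyalgia at all, or that TAU is wasted for harms. Neither follows, because the scales could show mean worsening in sleep, pain or mood against TAU. They are, however, designated efficacy measures and do not capture events.
- **The overlap with the FIQR is partial.** Correct. Of the item's three examples, sleep problems match directly, dizziness is at best close to balance problems, and headache is not in the FIQR list.
- **Leaving out 6 months fits an item about the treatment period.** Correct. A 6-month asking is a preference, not the repair of an error.
- **The article promises only perceived effects.** Also correct, so there is no contradiction in the text.
- **Supervised and home exercise might lead to different attribution.** A reader might infer this, but nothing in the article shows it, and the point does not rely on it.
- **A neutral item would be imprecise and would collect non-specific reports.** True, as the calculation shows. An imprecise controlled estimate still answers a question that the attributed count cannot.

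**Conclusion.** The point holds in limited form. As worded, the one dedicated harms item in the article cannot give a like-for-like randomised comparison of new symptoms or injuries, even if TAU participants are given it. Attributed counts in the active arms may be biased in either direction. This follows from the wording, the lack of blinding and the absence of a programme in TAU; it needs no assumed rate.

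The size of any bias cannot be derived from the documents. The 10% to 30% range and the ±15 to ±18 point precision rest on assumed rates of 30% and 40% and, for the range, on an assumed attribution share of 25% to 75%. The primary endpoint and the stated efficacy inferences are unaffected. This is a cheap improvement to how harms are measured.

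**What to change.** Replace the item with a neutral one, worded identically in all three arms: any new or clearly worsened symptom or injury since the last assessment, with type and severity. Ask it at 6 and 12 weeks, and preferably at the existing 6-month assessment, which comes before TAU participants are offered the programme. Keep the attribution question as a follow-up in the active arms. Report proportions by randomised arm with differences and 95% CIs, and state in advance that precision will be limited. Read the result alongside the symptom scales and the CSRI, which already cover average worsening and service use.

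The cost is one reworded item in an online battery, optionally one addition to the 6-month form, and one descriptive table. The downsides are more non-specific symptom reports to tabulate and the loss of exact continuity with the item used in the previous study.

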### 2.10 Physiological markers

Blood samples will be collected in vials which will be centrifuged and the resulting serum will be stored frozen at -80°C until analysis. All samples (pre and post) will be analyzed in a single analytical batch in order to reduce inter-assay variability (approximately 15%). Serum levels of the cytokines IL-6, CXCL8, IL-4, IL-10, IL-17A and hs-CRP will be assessed. For the quantification of cytokines, Milliplex^®^ reagents from MerckMillipore analyzed on a Luminex^®^ platform will be used. The highly sensitive Human High Sensitivity T Cell multiplex kit will be used (catalogue number: HSTCMAG28SPMX11). The hs-CRP will be quantified by turbidimetry on a Siemens Atellica autoanalyzer. BDNF levels will be evaluated using an ELISA kit (reference SEA011Hu-96T). Sample analysis will be performed by the Echevarne Laboratory. Detection concentration ranges: IL-6 (0.64–10,000 pg/ml), CXCL8 (0.64–10,000 pg/ml), IL-4 (0.64–10,000 pg/ml), IL-10 (2.6–40,000 pg/ml), IL-17A (1.3–20,000 pg/ml), hs-CRP (0.1–50 mg/L), and BDNF (31.2–2,000 pg/ml). Biomarkers will be assessed only at baseline and post-intervention because of the following reasons: a) evidence of changes in immune-inflammatory markers and BDNF levels after non-pharmacological interventions with a similar duration (Sanada et al., 2015; Montero-Marín et al., 2019; Pérez-Aranda et al., 2019); b) lower risk of sample loss (vs. assessing at 6 months); c) possibility to use pre-post change as a mediator of clinical changes at 6 months follow-up; and d) budget constraints.

### 2.11 Statistical analyses

SPSS v26.0, STATA v16.0 and Mplus v7.4 will be used for the statistical analyses. Descriptive statistics will be calculated for all variables and presented as means and standard deviations if continuous, or as absolute numbers and percentages (%) if categorical. The Levene test will be used to assess the equality of variances of continuous variables and Kolmogorov–Smirnov to test sample normality and distribution. One-way ANOVAs (with post hoc Tukey’s HSD or Games-Howell tests) for continuous values and χ2 tests with continuity corrections for categorical values will be computed on all baseline measures and socio-demographic variables to examine between-group differences at baseline.

#### 2.11.1 Analysis of clinical effectiveness

The primary effectiveness analysis will be conducted on an intention-to-treat (ITT) basis with the FIQR total score as a primary clinical endpoint (McCoy, 2017) and by linear mixed-effects regressions with restricted maximum likelihood (REML). REML accounts for the correlation between repeated measures for each individual and produces less biased estimates of variance parameters when using small sample sizes or unbalanced data (Egbewale et al., 2014). No imputation of missing data will be conducted, since it has been reported that multiple imputation is not necessary for all types of missing data (missing completely at random, missing at random, and missing not at random) before computing longitudinal mixed model analysis (Twisk et al., 2013). Unstandardized regression coefficients (B) and 95% confidence intervals (95% CIs) will be computed for the ‘group x time’ interaction between groups at 6-week, post-treatment and 6-month follow-up assessments. Cohen’s d will be calculated for each pairwise comparison, using the pooled baseline SD to weight the differences in the pre–post mean values and to correct for the population estimate (Morris, 2008). The rule of thumb for effect size interpretation will be the classical cutoffs for Cohen’s d of 0.20 = small, 0.50 = medium, and 0.80 = large. All secondary clinical endpoints will be analyzed using the same statistical procedure. Benjamini–Hochberg correction for multiple comparisons will be applied to control for false rate discovery (Glickman et al., 2014). All the analyses will be replicated using a “completers” approach including all participants who finished the study, and a per-protocol approach, taking into account only those patients who attended at least 75% of the sessions (9 out of 12).

In addition, to assess clinical significance of the improvement on the primary outcome (FIQR), all the participants will be allocated into the categories of “responder” and “non-responder” by using the criteria of presenting at least a 20% reduction in the pre–post FIQR total score or not, respectively (Bennett et al., 2009). This classification will be used to compute the number needed to treat (NNT) for each treatment when compared to the others. The NNT refers to the estimated number of patients who need to be treated with a new proposed treatment (i.e., rather than the control comparison treatment) for one additional patient to benefit. A 95% CI for each NNT will be calculated. This index allows findings from RCTs to be more meaningful to clinicians. Furthermore, in order to explore potential predictors of treatment response in each intervention arm, t-tests and χ2-tests will also be performed to assess potential baseline differences in sociodemographic, clinical and physiological variables between responders vs. non-responders within the FIBRO-Out and FIBRO-On arms. Finally, baseline differences between participants who completed all study assessments and those who did not will also be evaluated (with *t* and *χ2*-tests) to detect any potential attrition bias.

The differences between FIBRO-On and FIBRO-Out on perceived clinical improvement (assessed with PGIC and PSIC) and on treatment expectation/opinion (i.e., with the CEQ) will be computed using χ^2^ tests and Student’s *t* tests, respectively.

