There are also some potential limitations that should also be recognized in this RCT. One of the main risks of this project may be dropouts and non-adherence, which are expected to be higher than in previous studies that only evaluated the short-term efficacy of the interventions (Serrat et al., 2020; Serrat et al., 2021a; Serrat et al., 2021b; Serrat et al., 2022b). In this regard, since previous studies showed very high adherence to the programs (over 90%; Serrat et al., 2020; Serrat et al., 2022b), a dramatically high dropout in the present study is not expected; however, to limit the effect of these dropouts and lack of adherence in our results, we will conduct several sensitivity analyses (ITT, completers, per protocol analysis). We also have to note the lack of blinding of participants and therapists, which is a typical bias in any RCT including non-pharmacological treatments. Although a weekly questionnaire will be administered to check the adherence to FIBRO-On program (i.e., watching the videos), there is a risk that some participants in the FIBRO-On group do not watch the videos and inform differently. It is also relevant to highlight that this RCT will be carried out in a specialized unit of tertiary referral hospital in the context of clinical practice. Related to this, stricter inclusion/exclusion criteria could not be established due to pressures in daily clinical practice (i.e., most patients will be admitted). At the same time, this latter point may have a positive aspect by increasing the external validity of the study and so the generalization of the results into the “real” clinical practice.

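### Imputation is dismissed even for data missing not at random, and the named re-analyses cannot test the missing-at-random assumption on which the primary FIQR model rests

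*Protocol article*

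**What the plan says.** Section 2.11.1 analyses the primary endpoint, FIQR, on an intention-to-treat basis "by linear mixed-effects regressions with restricted maximum likelihood (REML"). It then fixes the missing-data rule: "No imputation of missing data will be conducted". The reason, taken from a cited methods paper, is that before a longitudinal mixed model "multiple imputation is not necessary for all types of missing data (missing completely at random, missing at random, and missing not at random").

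Two re-analyses are named in the same section. The first: "All the analyses will be replicated using a “completers” approach including all participants who finished the study". The second is per-protocol, with "only those patients who attended at least 75% of the sessions (9 out of 12"). The section also compares baseline characteristics of those who completed all assessments with those who did not, as a check for attrition bias.

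The Discussion gives these analyses their purpose: "to limit the effect of these dropouts and lack of adherence in our results, we will conduct several sensitivity analyses (ITT, completers, per protocol analysis"). It also expects more dropout and non-adherence than in earlier short-term trials of the programme. Section 2.3 plans for 20–25% dropout.

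**The concern.** Two questions are run together. One is whether imputing before a mixed model adds anything. Under MAR it largely does not, because the likelihood already uses each participant's observed visits. The other is whether the resulting estimate is valid. Under MNAR, where loss depends on the unseen FIQR score even after conditioning on what was observed, it generally is not, with or without standard imputation. Naming MNAR in the justification invites the reader to treat the second question as settled.

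The named checks do not reopen it. Completers drops partial data and so relies on stronger assumptions than the primary model. Per-protocol selects on attendance after randomisation. The attrition comparison looks only at baseline variables and cannot show dependence on outcomes that were never seen.

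Sections 2.13, 2.8.1 and 2.6 show why this matters here. Participants are not blinded, the primary outcome is self-reported, and the arms differ in what they demand. Loss related to lack of benefit, and differing by arm, is plausible, although the documents give no evidence that it will occur.

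**Working it through.** **Inputs from section 2.3.** Dropout 20–25%; d = 0.5 on FIQR, active arm against control, at post-intervention; alpha 0.05; power 0.80; 63 evaluable per arm. Two-sided testing is assumed.

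**The plan's own figure.** n = 2(1.960 + 0.842)² / 0.5² = 2 × 7.85 / 0.25 = 62.8, so 63 per arm. This reproduces, so d = 0.5 is a fair yardstick.

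**Step 1: delta adjustment.** Let p be the share lost in an arm and δ the amount, in SD, by which those lost do worse than MAR predicts. The overstatement of the effect is p(active)·δ(active) − p(TAU)·δ(TAU). The documents do not give δ, so a range is shown, with δ(TAU) = 0:

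| δ in active arm (assumed) | 20% loss | 25% loss | A reported 0.50 would be |
|---|---|---|---|
| 0.2 | 0.20 × 0.2 = 0.04 | 0.25 × 0.2 = 0.05 | 0.46–0.45 |
| 0.5 | 0.20 × 0.5 = 0.10 | 0.25 × 0.5 = 0.125 | 0.40–0.375 |
| 1.0 | 0.20 × 1.0 = 0.20 | 0.25 × 1.0 = 0.25 | 0.30–0.25 |

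If p and δ are the same in both arms, the two terms cancel and the bias is zero.

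**Step 2: does comparison with completers reveal the problem?** This was examined by large-sample simulation: four visits, SD 1, true effect −0.5 SD at 12 weeks and 6 months, monotone dropout of 20% or 25% per arm, between-visit correlation 0.6, dropout log-odds slope of 1 per SD. The correlation, slope and mechanisms are assumptions. Bias at 6 months in SD is shown for 20% / 25% loss; negative values exaggerate benefit.

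| Mechanism in the active arm | Mixed model | Completers |
|---|---|---|
| MAR, last observed level | −0.002 / −0.003 | +0.024 / +0.028 |
| MAR, last observed change | −0.001 / −0.001 | −0.054 / −0.067 |
| MNAR, unseen change | −0.062 / −0.085 | −0.106 / −0.139 |
| MNAR, unseen level | −0.067 / −0.081 | −0.031 / −0.034 |

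With the same MNAR mechanism in both arms, both biases were about zero. The ordering of the four rows was the same at correlations 0.4 and 0.8; the symmetric case was run only at 0.6.

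The two analyses can differ when the mixed model is unbiased (rows 1 and 2) and when it is biased (rows 3 and 4), and completers can lie on either side of it. The gap between them therefore does not show whether MAR fails. Dividing the mixed-model bias in rows 3 and 4 by the loss gives an implied δ of about 0.31 to 0.34 (for example 0.062 / 0.20 = 0.31 and 0.085 / 0.25 = 0.34), inside the range of step 1.

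**Step 3: per-protocol.** TAU has no sessions, so the sensible reading applies the 9-of-12 rule to the active arms and keeps TAU whole. If a share q of the active arm is excluded and attendance correlates r with better outcome, the retained mean shifts by r·φ(z)/(1 − q), where z is the normal cut-off for q. At q = 0.10 and r = 0.1 this is 0.1 × 0.175 / 0.90 = 0.02. At q = 0.25 and r = 0.3 it is 0.3 × 0.318 / 0.75 = 0.13. A true 0.50 becomes 0.52 to 0.63 through selection alone. Both q and r are assumptions.

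**The case against.** The strongest reply is that section 2.11.1 says less than is held against it. It reports that imputation is unnecessary; it does not say that the model is unbiased under MNAR. Not imputing is defensible, since the mixed model uses partial data and a standard MAR-based imputation would not repair MNAR. This stands, and the point is therefore not that imputation should have been planned for FIQR.

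A second reply is that MNAR sensitivity analyses are often left to the statistical analysis plan. That would answer a complaint about an omission. Here the article states a rationale that covers MNAR, names its checks, and says what they are for. Those statements need correcting whatever the analysis plan contains.

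A reader might infer more than the documents support:

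- *Completers and per-protocol are always more biased than the primary analysis.* In the simulation completers was less biased when MNAR loss followed the outcome level.
- *The planned checks would show nothing.* A discrepancy could appear; it just could not be attributed to MNAR.
- *The trial will be biased by the amounts shown.* They assume a departure in one arm only. The Discussion cites adherence above 90% in earlier studies, and nothing says that people who stop sessions also stop completing assessments.
- *The 9-of-12 rule deletes TAU.* That reading is strained; the rule plainly concerns arms with sessions. The wording only needs to say so.

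**Conclusion.** The point holds in a limited form. The justification for not imputing extends to MNAR, where the primary model is not valid in general, and the analyses presented as limiting the effect of dropout rest on stronger assumptions and cannot test departure from MAR. The baseline attrition comparison cannot do so either.

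The potential size ranges from nothing, if the departure is equal across arms, to half of the planned effect (0.25 / 0.5) at 25% loss and δ = 1.0. At δ = 0.5 it is a fifth to a quarter (0.10–0.125 out of 0.5). These figures depend on δ, which the documents do not give. They show why a sensitivity analysis over δ is needed and are not a prediction. The choice of model and the decision not to impute can stay.

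**What to change.** 1. In section 2.11.1, delete the MNAR rationale and state that the primary mixed model assumes MAR.
2. Add an MNAR sensitivity analysis of FIQR: a delta tipping-point analysis with δ varied separately by arm, a reference-based analysis in which active-arm dropouts are treated as TAU-like, or both.
3. Keep completers and per-protocol as supplementary, and reword the Discussion so that they are not presented as protection against dropout bias.
4. State that the 9-of-12 rule applies to the active arms only, with FIBRO-On exposure counted by the weekly module questionnaires completed (section 2.6.2), whose known weakness the Discussion already admits. State also that the comparison of adherers with unselected TAU is not a randomised comparison.

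A complier-average causal effect is optional. It answers a different question, has assumptions of its own, and does not deal with missing outcomes.

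The cost is revised wording and a little programming, with no new data, and it should be settled before outcome data are examined. The drawback is that the robustness statement may turn out less favourable.
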